#### Analysis for the primary and secondary endpoints

The aim of the study is to compare the use of the two therapies in terms of a treatment strategy. The difference in the ESS should therefore be determined without taking into account possible treatment discontinuations or compliance problems. For this reason, the analysis is conducted in a modified intention-to-treat population, which consists of all FAS patients with at least one value of the primary endpoint after baseline.

The *primary endpoint* is analysed using a linear mixed model. The model should contain fixed effects for the intervention, the phase, the interaction between therapy and phase (including the carry-over effect) and the baseline measurement of the ESS as well as the baseline AHI. Both the centre effect and the patient effect are modelled as random effects. The one-sided *p*-value corresponding to the hypothesis specified above, the estimated difference in ESS between the two treatments, and the corresponding one-sided confidence interval are reported. The one-sided *p*-value is calculated from the *p*-value of the above model either as p/2 or as 1-p/2 depending on the sign of the estimator. Details of the model, imputation of missing values, and sensitivity analysis are provided in the SAP.

The *secondary* quantitative endpoints are analysed using analogous models, with the difference that the baseline value of the endpoint under consideration is included in the model as a fixed effect instead of the baseline ESS. Analogous to the analysis of the primary endpoint, the p-value, the estimated difference, and the associated 95% two-sided confidence interval are also specified here. The analysis of dichotomous secondary endpoints is performed using mixed logistic regression models with the fixed effects for therapy, phase, and phase times therapy interaction as well as random effects for centre and patient. The analysis of count data, e.g. AHI, is performed with mixed Poisson models or, if necessary due to overdispersion, with negative binomial models with the fixed effects for treatment, phase, and phase times treatment interaction as well as random effects for centre and patient.

The secondary endpoints are analysed using two-sided tests at a significance level of 5%; all analyses of the secondary endpoints are exploratory.

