**Methods:**

This is a multicentre, non-inferiority, open-label randomised, cross-over clinical trial. Patients with mild to moderate POSA and daytime sleepiness (according to Epworth Sleepiness Scale (ESS) > 10 points) will be randomised with a 1:1 allocation ratio, stratified by centre and AHI, to start with either PAP therapy or SPT and treated for 12 weeks. After a wash-out period of two weeks, they will switch to the other therapy for 12 weeks. The primary outcome is daytime sleepiness measured by the ESS at the end of each treatment phase. Analysis will be done in the intention-to-treat population using a linear mixed-effects model containing the intervention, the phase, the interaction between therapy and phase (including the carry-over effect) and the baseline measurement of the ESS and AHI as fixed effect, and centre and patient as random effects. A one-sided test at significant level of 2.5% will be used to test the non-inferiority of SPT with a non-inferiority margin of 1.35. Based on a sample size calculation with a one-sided one-sample t-test at significant level of 2.5%, assuming a standard deviation of 4, a total of 418 patients should be included to reach 80% power when SPT is only slightly inferior to PAP therapy (difference 0.8 resulting in a delta of 0.55 (1.35-0.8)). Assuming a 5% drop-out rate, 220 patients per sequence should be included. Possible futility stopping is planned at an interim analysis after 300 patients.

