### Sample size {14}

The aim of the study is to show that SPT is not inferior to PAP therapy in terms of daytime sleepiness measured with the ESS. A difference of 1.35 between the two means is proposed as the non-inferiority threshold, i.e. the hypothesis pair:$$H_0:\mu_{SPT}-\mu_{CPAP}\geq1.35\;vs.\;H_1:\mu_{SPT}-\mu_{CPAP}<1.35$$should be tested with a one-sided test at significance level of 2.5%.

This means that under the alternative hypothesis, the ESS value measured under SPT may not be more than 1.35 points higher on average than the ESS value under PAP therapy. The choice of the value for the non-inferiority margin is justified as follows: The study by Crook et al. investigated the size of the clinically relevant difference for the ESS. Depending on the method used, the difference was between 1 and 4.21 [12]. In other non-inferiority studies, a difference of 1.5 or 2 points was often chosen as the non-inferiority threshold [13]. One meta-analysis showed a difference between PAP vs. no therapy of 2.4 points (95% CI, 1.9 to 2.8) [14]. However, a more recent meta-analysis showed that this difference depends, among other things, on the baseline ESS and AHI. For example, a difference of 1.34 (0.68 to 1.99) was found for a baseline ESS > 10 points and AHI 5 to < 15/h and 2.22 (2.13 to 2.30) for an AHI 15/h to < 30/h [15]. Therefore, the size of the non-inferiority margin of 1.35 provided in the documents of Federal Joint Committee seemed appropriate to ensure at least a difference compared to no therapy in the planned study population.

Hence, sample size calculation was done using a one-sided one-sample *t*-test at a significance level of 2.5% and to achieve a power of 80% to test the above hypotheses. It was assumed that the difference between SPT and PAP is 0.8 points. Sample size calculation for a δ of 0.55 points (1.35–0.8), assuming a standard deviation of 4, results in a required sample size of 418 patients in total, i.e. 209 per sequence. A drop-out rate of 5% is assumed according to the studies by Berry and Mok, i.e. revocation or completely missing data after baseline [6, 13]. Therefore, a total of 440 patients, i.e. 220 per sequence, will be recruited into the study. Further missing values do not affect the sample size, as they will be replaced according to the analysis strategy.

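### The primary model carries a therapy-by-phase interaction and does not say which treatment contrast is tested; one natural reading is a phase-1 between-patient comparison with roughly 20-40% power instead of 80%

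*Protocol article*

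**What the plan says.** The section on the analysis of the primary and secondary endpoints specifies a linear mixed model with "fixed effects for the intervention, the phase, the interaction between therapy and phase (including the carry-over effect"), plus baseline ESS and baseline AHI, and random effects for centre and patient. The Methods part of the abstract repeats "the interaction between therapy and phase (including the carry-over effect"). The one-sided p-value is obtained by halving the model's p-value, or taking one minus half, according to the sign of the estimator. No contrast, factor coding or averaging over phases is named. The Statistical methods section names R as the software. Further model details are left to the SAP.

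Under Sample size {14}, "A difference of 1.35 between the two means is proposed as the non-inferiority threshold". The "sample size calculation was done using a one-sided one-sample" *t*-test, "assuming a standard deviation of 4", and "It was assumed that the difference between SPT and PAP is 0.8 points". The aim was "to achieve a power of 80% to test the above hypotheses", which led to 418 evaluable patients, 209 per sequence. A one-sample test in a cross-over works on within-patient differences, so the SD of 4 acts as the SD of the paired difference.

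Trial design {8} describes two sequences and two 12-week phases. It justifies the two-week wash-out by earlier studies that had shorter or no wash-out and showed no carry-over.

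**The concern.** Two sequences and two phases give four cell means. Intercept, intervention, phase and their interaction use all four degrees of freedom, so the interaction is the sequence contrast under another name and is inseparable from carry-over. Once it is in the model, the treatment effect is no longer a single quantity. It can be the effect at one phase or an average over both, and these have very different standard errors.

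The article's wording leaves room for the less precise choice. It describes the interaction as containing carry-over, and a treatment effect adjusted for carry-over in this design rests on phase 1 alone. It takes the p-value from the model, and R's default treatment coding with phase 1 as reference makes the intervention coefficient the phase-1 effect. On that reading the only confirmatory test would use a different estimator from the one that was sized, and the choice of contrast could decide whether non-inferiority is concluded.

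The interaction also brings the primary estimate no benefit. It does not remove carry-over bias from the phase-averaged difference, and that difference has the same standard error with or without it.

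**Working it through.** **Inputs from Sample size {14}:** one-sided alpha 2.5%, margin 1.35, assumed difference 0.8, hence distance to the margin 1.35 - 0.8 = 0.55; SD 4; 418 evaluable (209 per sequence). **Not in the document, so assumed:** a within-patient correlation r of 0.3 to 0.7, taken to be the same between baseline and each phase as between the two phases.

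**1. The plan's own figure.** A one-sample *t*-test (noncentral *t*) with distance 0.55 and SD 4 needs n = 418, with power 80.1%. Drop-out: 418 / 0.95 = 440. Both match the article. In normal approximation, SE = 4 / sqrt(418) = 0.196 and power = Phi(0.55/0.196 - 1.96) = 80.3%.

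**2. What the coefficients mean.** Let T = 1 for SPT, P = 1 for phase 2, and mean = b0 + b1·T + b2·P + b3·T·P. Write S1 and S2 for the SPT means in phases 1 and 2, and A1 and A2 for the PAP means. Then:

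- b1 = S1 - A1: the phase-1 difference, between patients.
- b3 = (S2 - A2) - (S1 - A1) = (A1 + S2) - (S1 + A2): the difference between the two sequences in their totals, hence the aliasing with sequence and carry-over.
- b1 + b3/2 = half of [(S1 - A2) + (S2 - A1)]: the average of the two sequences' within-patient differences.

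**3. Standard error of the phase-averaged contrast.** Variance = (1/4)(16/209 + 16/209) = 16/418, so SE = 0.196 and power 80.3% at every correlation. Removing the interaction gives the same SE.

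**4. Standard error of the phase-1 coefficient.** The single-phase SD is s = 4 / sqrt(2(1 - r)). Without baseline adjustment, SE = s·sqrt(2/209). With adjustment for baseline ESS, SE = s·sqrt(1 - r²)·sqrt(2/209). Power = Phi(0.55/SE - 1.96).

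| r | s | SE, unadjusted | power | SE, baseline-adjusted | power |
|---|---|---|---|---|---|
| 0.3 | 3.38 | 0.331 | 38% | 0.315 | 41% |
| 0.4 | 3.65 | 0.357 | 34% | 0.327 | 39% |
| 0.5 | 4.00 | 0.391 | 29% | 0.339 | 37% |
| 0.6 | 4.47 | 0.437 | 24% | 0.350 | 35% |
| 0.7 | 5.16 | 0.505 | 19% | 0.361 | 33% |

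Example at r = 0.5, adjusted: s = 4; 4 × sqrt(0.75) = 3.46; SE = 3.46 × sqrt(2/209) = 0.339; Phi(0.55/0.339 - 1.96) = 36.8%.

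**5. Checks.** Generalised least squares for the 2×2 design gave the same standard errors: 0.391 (unadjusted) and 0.339 (adjusted) for 0/1 coding with the interaction at r = 0.5, and 0.196 for sum-to-zero coding or no interaction. A mixed-model simulation of 60 trials, with baseline as covariate, gave mean standard errors of 0.339 and 0.196. That is too few runs to estimate power, but enough to confirm the standard errors.

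**The case against.** The strongest reply is that the article never commits to the phase-1 coefficient. The hypotheses under Sample size {14} concern one overall difference with no phase index, the analysis section reports one difference between the two treatments, and the abstract measures the outcome at the end of each phase. All of this favours an overall comparison. Naming R does not fix a coding. The null value is 1.35, so the p-value that R prints for a coefficient (against zero) cannot itself be the stated test, and some constructed contrast or shift is needed anyway. Which contrast is reported is commonly left to the SAP, and the article refers model details there.

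Much of this stands. A reader might infer that power falls from 80% to about 36% because the interaction is in the model, or that the phase-2 data are discarded. The document supports neither: the same model with a phase-averaged contrast keeps 80%, and nothing confines the primary test to phase 1. A single figure such as 36% also needs a correlation that the document does not give.

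What does not stand is that the matter is wholly deferred. The interaction is a term that the article itself places in the confirmatory model, with a reference to carry-over that invites a carry-over-adjusted reading. The need for a shift to 1.35 does not settle which quantity is shifted.

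**Conclusion.** The point holds in conditional form. The confirmatory model contains a term that is aliased with carry-over and does not improve the primary estimate, and the tested contrast is not named. If the effect is read as the default-coded intervention coefficient or as carry-over-adjusted, it is the phase-1 comparison of 209 against 209 patients. Its SE is then 0.32 to 0.51 instead of 0.196, and power at a true difference of 0.8 is about 19-41%. This range rests on the assumed correlations of 0.3 to 0.7, on whether baseline ESS is adjusted for, and on the SD of 4 being that of the paired difference. If the effect is the phase-averaged contrast, the stated 80% is intact. The calculation of 418 and 440 is itself correct.

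**What to change.** Preferred: specify the primary model with therapy, phase, baseline ESS and baseline AHI as fixed effects and patient and centre as random effects, without the interaction. Report the therapy-by-phase (carry-over) term from a separate supportive model, and state that it does not decide the primary result.

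Alternative, if the term must stay: state that the quantity compared with 1.35 is the equally weighted average of the two phase-specific SPT minus PAP differences, for example through sum-to-zero coding or an explicit contrast.

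Apply the same choice to the secondary models, which carry the same interaction; less depends on it there because those analyses are exploratory. The cost is a change of wording in the protocol and SAP, to be made before the analysis starts. No additional data or patients are needed.

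### The formula for the primary one-sided p-value leaves out the 1.35 margin; applied literally it tests superiority, contradicting the non-inferiority hypothesis it is meant to serve

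*Protocol article*

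**What the plan says.** The section Sample size {14} fixes the hypothesis: "A difference of 1.35 between the two means is proposed as the non-inferiority threshold". H0 is μ_SPT − μ_CPAP ≥ 1.35 against H1 < 1.35, and this "should be tested with a one-sided test at significance level of 2.5" per cent. The Abstract states the same margin and level.

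The section Analysis for the primary and secondary endpoints describes a linear mixed model. Fixed effects are intervention, phase, their interaction, baseline ESS and baseline AHI; centre and patient are random. The section announces a one-sided p-value for the hypothesis already stated, an estimated treatment difference and a one-sided confidence interval. It then says that the p-value is derived from the p-value "of the above model either as p/2 or as 1-p/2 depending on the sign of the estimator". No offset, shifted contrast or margin appears in the model or in this rule.

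The opening of Statistical methods counts a one-sided p-value of at most 2.5% as significant. No sentence ties the conclusion to a comparison of the confidence limit with 1.35.

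**The concern.** The p-value that a mixed model ordinarily reports for a treatment term tests a difference of 0. Halving it, or taking 1 − p/2, by the sign of the estimate gives a one-sided test against 0. The sign of the estimate shows its side of 0, not its side of 1.35. So the formula does not deliver the p-value announced in the sentence before it.

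This formula produces the only significance criterion stated for the confirmatory test. Two results reported side by side could then disagree: an upper confidence limit below 1.35 next to a p-value close to 1. The direction is also open, because the article does not define the estimator as SPT − PAP at this point or say which sign gets p/2. That matters more than usual because the analysing statistician works with uninformative group codes.

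**Working it through.** **Inputs, all from Sample size {14}**
- Margin 1.35; one-sided α = 2.5%.
- True difference: "It was assumed that the difference between SPT and PAP is 0.8 points".
- Distance to the margin: 1.35 − 0.8 = 0.55.
- SD and N: "assuming a standard deviation of 4, results in a required sample size of 418 patients in total".
- Method: "sample size calculation was done using a one-sided one-sample" t-test, "to achieve a power of 80% to test the above hypotheses".

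**1. The plan's own figure.** A one-sample noncentral t calculation with δ = 0.55, SD 4 and one-sided α 0.025 gives N = 418 with power 80.1% (normal approximation: 416). Also 418/0.95 = 440. The sample size is right, and it is built on the margin test.

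**2. Standard error.** SE = 4/√418 = 0.1956.

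**3. Estimate needed for success**
- Margin test, (estimate − 1.35)/SE ≤ −1.96: estimate ≤ 1.35 − 1.96 × 0.1956 = 0.97.
- Literal rule, p/2 for negative estimates, estimate/SE ≤ −1.96: estimate ≤ −1.96 × 0.1956 = −0.38.

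**4. Probability of success (normal approximation)**
- Margin test: Φ((1.35 − d)/SE − 1.96), where d is the true difference.
- Literal rule: Φ(−d/SE − 1.96).

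| True SPT − PAP | Margin test | Literal rule |
|---|---|---|
| 1.35 | 2.5% | 4 × 10⁻¹⁹ |
| 0.8 | 80% | 7 × 10⁻¹⁰ |
| 0.5 | 99.1% | 3 × 10⁻⁶ |
| 0.25 | >99.9% | 0.06% |
| 0 | >99.9% | 2.5% |
| −0.55 | >99.9% | 80% |

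At d = 0.8 the literal rule gives Φ(−4.09 − 1.96) = Φ(−6.05), about 7 × 10⁻¹⁰. In 1,000,000 simulated estimates it never rejected, while the margin test rejected in 80.4%. With N = 418 and SD anywhere from 3 to 6, the literal rule stays below 0.0002% at d = 0.8.

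**5. One trial result under both rules.** Take an estimate of exactly 0.8.
- Upper one-sided 97.5% limit: 0.8 + 1.96 × 0.1956 = 1.18, below 1.35, so non-inferior.
- Margin p-value: Φ((0.8 − 1.35)/0.1956) = Φ(−2.81) = 0.0025.
- Literal rule: two-sided p against 0 is 0.00004, the estimate is positive, so 1 − p/2 = 0.99998.

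**6. Opposite sign assignment.** If p/2 went to positive estimates, the rule would declare success with probability Φ(d/SE − 1.96): 98.3% at d = 0.8 and more than 99.9% at d = 1.35, where the error rate should be 2.5%.

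**The case against.** The best defence is that the intent is plain. The Abstract, the hypothesis pair and the sentence just before the formula all name the margin hypothesis. The disputed sentence can be read as a generic conversion from a two-sided to a one-sided p-value. That conversion is correct if the contrast has been shifted by 1.35 and the estimator means the shifted one. The confidence interval reported alongside would give the right answer if compared with 1.35. The article also leaves details of the model to the SAP, which is not shown and may specify the shift.

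Most of this stands, and it limits the consequence. A reader might infer that the trial has practically no power, or that it is designed as a superiority trial. The documents do not support either: the sample size is correct for the margin test, and the loss appears only if the formula is applied as written. A reader might also infer a risk of false non-inferiority claims. With p/2 for negative estimates the reverse holds, since the rule is far too strict; that risk exists only with the opposite assignment.

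The defence does not make the sentence right. The article does not leave the formula out: it prints one, applies it to a model without the margin, and names no shift. Deferral to the SAP excuses an omission, but not a statement that conflicts with the hypothesis.

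One further caveat stands. The SE of 0.196 comes from the one-sample planning calculation and not from the mixed model, so the cut-offs 0.97 and −0.38 are approximate.

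**Conclusion.** Wrong as written, and to be corrected before the analysis. The section on the primary analysis contradicts itself: it announces a p-value for the 1.35 hypothesis and prints a formula that never uses 1.35 and leaves the direction open.

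If the formula is followed literally with p/2 for negative estimates, the bar for success moves by the whole margin, from about 0.97 to about −0.38. The planned 80% at a true difference of 0.8 becomes practically zero, and two exactly equal therapies would succeed 2.5% of the time instead of more than 99.9%. These figures rest on N = 418, SD 4 for the within-patient difference, and a mixed-model SE close to the planning SE. The near-zero result at 0.8 does not depend on the exact SD.

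The sample size needs no change. Nor does the interim hypothesis: Interim analyses {21b} already refers to 1.35, and its 80% power at 300 patients fits that margin ((2 − 1.35)/(4/√300) = 2.81 standard errors).

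**What to change.** Replace the sentence on p/2 and 1 − p/2 with:

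> With the difference defined as SPT − PAP, the one-sided p-value is P(T_df ≤ (estimate − 1.35)/SE) from the mixed model. Equivalently, it is obtained from the two-sided p-value of the test of difference = 1.35, as p/2 if estimate − 1.35 is negative and 1 − p/2 otherwise. Non-inferiority is concluded if the upper limit of the one-sided 97.5% confidence interval is below 1.35.

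Shifting the model by 1.35 and reading off its p-value is not enough, because that p-value is two-sided. An estimate of 1.9, with SPT clearly worse, lies as far from 1.35 as an estimate of 0.8 does, and both would show p of about 0.005. The halving by the sign of estimate − 1.35 must therefore stay.

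The cost is one sentence in the protocol, and the same in the SAP if it repeats the formula. No patients, data or changes to the design are needed. It should be in place before the statistician sees outcome data, so that nobody has to choose between two conflicting readings afterwards.

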## Abstract

**Background:**

First-line therapy for patients with clinically relevant obstructive sleep apnoea (OSA) is positive airway pressure therapy (PAP). At least one half of patients with mild to moderate OSA (apnoea-hypopnoea-index (AHI) 5-30/h) have positional OSA (POSA), where apnoea occurs mostly in supine sleep. These patients might benefit from sleep-position therapy (SPT) which should reduce sleeping time spent in a supine position. Until now, it is unclear whether SPT is non-inferior to PAP therapy for symptom relief in these patients.

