## Introduction

### Background and rationale {6a}

Obstructive sleep apnoea (OSA) is the most common organic sleep disorder. During sleep, the relaxation of the muscles leads to a narrowing or collapse of the upper airways. In addition to the occurrence of snoring, this is accompanied by restricted or interrupted ventilation of the lungs. These events are called hypopnoea and apnoea. The associated oxygen drops in the blood lead to short arousals and thus to an interruption of sleep. Even if the arousals are often not remembered the next day, around 1/3 of OSA patients report relevant daytime sleepiness. Subjective daytime sleepiness can be determined using internationally validated questionnaires such as the Epworth Sleepiness Scale (ESS) [1]. In the medium to long term, the stress reactions caused by sleep-related breathing disorder also led to an increased risk of cardiovascular diseases, depression, and dementia [2]. After a specific medical history, patients with suspected OSA get an overnight portable breathing monitoring system (polygraphy = PG) at their homes in accordance with the German guideline on methods of contract medical care issued by the German Federal Joint Committee (G-BA) [3]. If there is a hint of a sleep-related breathing disorder, but a final diagnosis cannot be proven based on portable monitoring, the diagnosis is confirmed by a fully attended polysomnography (PSG) in a sleep laboratory.

The severity of OSA is defined by the apnoea-hypopnoea index (AHI)—i.e. the number of breathing disturbances per hour of sleep. Here, the normal value is an AHI < 5/h. A mild OSA is diagnosed with an AHI of 5– < 15/h, a moderate OSA with an AHI of 15– < 30/h, and a severe OSA with an AHI ≥ 30/h. Based on the AHI, current epidemiological studies show a high prevalence of OSA. In Germany, for example, around 14 million people are estimated to show an AHI ≥ 15/h and even around 26 million an AHI ≥ 5/h [4]. According to the S3 guideline of the German Society for Sleep Research and Sleep Medicine (DGSM), treatment is indicated for an AHI ≥ 15/h regardless of the associated symptoms or for mild OSA (AHI 5– < 15/h) with associated symptoms or an increased cardiovascular risk due to existing comorbidities [5].

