## Outcomes {12}

The primary endpoint of the study is the change in subjective daytime sleepiness, measured with the ESS [1] before and 12 weeks after the start of the respective intervention. The following parameters are to be analysed as secondary endpoints:

Subjective sleep quality according to the Pittsburgh Sleep Quality Index (PSQI) [8]Objective sleep parameters derived from PSG in comparison to the initial diagnostic PSG-examination: Total AHI, proportion of sleep time in supine position, AHI in supine position, AHI in non-supine position, oxygen desaturation index (ODI), mean oxygen saturation (SaO2 mean), minimum oxygen saturation (SaO2 min), time with oxygen saturation < 90% (T90) (all assessed by pulse oximetry), Total sleep time (TST), sleep onset latency, total wake time after first falling asleep (WASO), sleep efficiency (SE), sleep times in sleep stages N1, N2, N3 and REM, heart rate variability, arousal index, respiratory disturbance index (RDI) [9]Health-related quality of life according to the Functional Outcomes of Sleep Questionnaire (FOSQ-10) [10]Quality of life according to EuroQol-5D-5L (EQ-5D-5L) [11]Adverse events (AEs) according to standardised severity classification and treatment discontinuations due to AEsUsage data of SPT or PAP therapy to evaluate therapy adherence and to analyse a usage-related therapy effect (here: daytime sleepiness), as sufficient and regular use of sleep apnoea therapy is a prerequisite for the therapy effect in relation to the baseline. For this purpose, a corresponding effectiveness analysis should be carried out (analysis of the actual utilisation time of the respective intervention in relation to the mean, specified total sleep time in the corresponding intervention phase). The utilisation data can be read out easily and securely via the SPT device application or via the PAP device’s internal data stored on a SD card or transmitted by telemonitoring.

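### AHI is a rate per hour by the protocol's own definition, but it is assigned to count models with no sleep-time exposure listed; supine AHI is the most exposed endpoint

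*Protocol article*

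**What the plan says.** The section on analysis of the primary and secondary endpoints, under {20a}, separates three kinds of secondary endpoint. For quantitative ones, "the baseline value of the endpoint under consideration is included in the model as a fixed effect instead of the baseline ESS". Dichotomous ones get mixed logistic models. For the third kind, "The analysis of count data, e.g. AHI, is performed with mixed Poisson models" or, where overdispersion requires it, "negative binomial models with the fixed effects for treatment, phase, and phase times treatment interaction as well as random effects for centre and patient". Neither sleep time nor a baseline value appears among these terms.

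Background and rationale {6a} defines AHI as "the number of breathing disturbances per hour of sleep". Outcomes {12} lists the affected endpoints, among them "Total AHI, proportion of sleep time in supine position, AHI in supine position, AHI in non-supine position, oxygen desaturation index (ODI"), and describes them as "Objective sleep parameters derived from PSG in comparison to the initial diagnostic PSG-examination". The abstract describes "sleep-position therapy (SPT) which should reduce sleeping time spent in a supine position".

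All secondary analyses are two-sided at 5% and exploratory. The opening of the statistical methods section leaves details to a SAP that is not shown.

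**The concern.** A Poisson model ties the variance of an observation to its mean. That fits a number of events. It does not fit events divided by hours, where the variance also depends on how many hours were recorded. Entering AHI itself as the count amounts to treating every recording as one hour long.

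Two things follow. The standard error is calibrated to the wrong quantity, and recordings of different length carry the same weight. The second matters most for supine AHI, because the denominator shrinks in one treatment by design. The AHI endpoints are objective measurements in an open-label trial whose primary outcome is self-reported, so their intervals will be read with interest even though they are exploratory.

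**Working it through.** The document gives no figure for the AHI analysis, so there is none to reproduce.

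**Inputs from the protocol.** AHI is a rate per hour; the model terms are as listed above; 418 patients in a two-period cross-over (Sample size {14}); at least 30% supine sleep at entry (Eligibility criteria {10}).

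**Assumed inputs.** Total sleep 6 h (7 h as a variant). Supine time 0.1, 0.25 or 0.5 h under SPT and 2 h under PAP; 30% of 6 h is 1.8 h, so 2 h is close to the entry minimum. Total AHI 6 vs 6 or 8 vs 3 per hour (SPT vs PAP); supine AHI 20 vs 20 or 20 vs 4. Night-to-night coefficient of variation (CV) of the true rate 0 to 0.8.

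**Step 1, pure Poisson events.** If the count is Poisson(rate × T), AHI = count/T has variance rate/T. A Poisson model on AHI assumes variance = rate. The ratio of model SE to true SE is √T: √6 = 2.45 and √7 = 2.65.

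**Step 2, night-to-night variation.** The variance of AHI becomes rate/T + CV² × rate², so for one patient the ratio is 1/√(1/T + CV² × rate). At 6/h and 6 h it equals 1 when CV² = (1 − 1/6)/6 = 0.139, that is CV ≈ 0.37. Below that the Poisson SE is too large; above it, too small.

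**Step 3, simulation of total AHI.** 418 patients, 2,000 runs per scenario, within-patient Poisson log rate ratio on AHI without offset, with between-patient and sleep-time variation:

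| CV | Model SE / true SE, 6 vs 6 | Coverage of 95% interval | Model SE / true SE, 8 vs 3 | Coverage |
|---|---|---|---|---|
| 0 | 2.44 | 100% | 2.46 | 100% |
| 0.3 | 1.05 | 96% | 1.20 | 98% |
| 0.5 | 0.69 | 82% | 0.79 | 88% |
| 0.8 | 0.45 | 63% | 0.53 | 70% |

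**Step 4, supine AHI.** For a true rate of 20/h, the sampling SE of one recording is √(20/T): √(20 × 6) = 10.95/h from 10 minutes and √(20/4) = 2.24/h from 4 hours. Without exposure the model weights both alike. Same simulation:

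| Supine AHI, SPT vs PAP | Supine time, SPT vs PAP | Ratio (coverage), CV 0 | Ratio (coverage), CV 0.8 |
|---|---|---|---|
| 20 vs 20 | 0.1 vs 2 h | 0.43 (59%) | 0.21 (33%) |
| 20 vs 20 | 0.25 vs 2 h | 0.67 (81%) | 0.23 (37%) |
| 20 vs 20 | 0.5 vs 2 h | 0.91 (93%) | 0.24 (35%) |
| 20 vs 4 | 0.1 vs 2 h | 0.68 (82%) | 0.37 (54%) |
| 20 vs 4 | 0.25 vs 2 h | 1.00 (95%) | 0.39 (55%) |

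These ratios are for the Poisson model. The negative binomial fallback was not simulated.

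**Step 5, offset and baseline.** Poisson mixed models with a patient random intercept, pure Poisson events at about 6 h, 12 data sets. With event counts and a log sleep-time offset, the mean SE of the log rate ratio is 0.01185 (empirical SD 0.0104, imprecise with 12 data sets). With AHI rounded to integers and no offset it is 0.02907, and 0.02907/0.01185 = 2.45, as in step 1. Adding baseline to the offset model leaves the SE at 0.01185 and the estimate at 0.498.

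**The case against.** The strongest reply is that an offset is not an effect. It has no estimated coefficient, so a list of fixed and random effects need not show it, and a count model for AHI is compatible with event counts plus log sleep time. The SAP may specify exactly that. This stands as far as it goes: a reader might infer that the trial will certainly be analysed without exposure, and the document does not show that. What remains is a stated rule that names the rate itself as the count, against the document's own definition. A SAP that follows this wording would model the index.

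The negative binomial fallback also counts for the plan. At higher CVs, and for short supine recordings, it would replace the Poisson model, so the low coverages above overstate what the plan would deliver there. But it can only add variance. It cannot shrink an SE that is too large, and it does not know how long each recording was.

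Three stronger readings are tempting and fail:

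- A reader might infer that leaving out baseline AHI makes the standard errors wrong. It does not: with both periods observed, the patient effect absorbs it (step 5). It is an inconsistency with the rule for quantitative endpoints and with the definition of the PSG endpoints relative to the diagnostic PSG, and may cost some efficiency for incomplete pairs.
- A reader might take the factor of about 2.45 as the general size of the error. It holds only without night-to-night variation.
- A reader might extend the point to ODI, RDI and arousal index. The protocol names only AHI as count data.

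Two more points stand in part. A patient with no supine sleep has no supine AHI, and section {20c} says missing secondary values are not replaced, so that patient would simply drop out; very short supine time is not covered by this. And weighting by supine hours is not neutral, because it favours patients in whom SPT failed to prevent supine sleep. That bears on how supine AHI is reported, not on whether the index is a count.

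**Conclusion.** The point holds in limited form. The protocol labels a per-hour rate as count data and lists no exposure. Analysed that way, the variance is mis-specified, with no fixed direction for total AHI: from 2.4 times too large to less than half the true SE under the Poisson model, depending on a night-to-night variation that the document does not give. For supine AHI the Poisson SE was mostly too small in the scenarios tried, but this rests on assumed supine times and rates, and in one scenario it was correct. Supine AHI is the most exposed endpoint because SPT acts on its denominator.

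The consequence is confined to exploratory secondary endpoints. The ESS comparison, the margin, the sample size and the futility rule are untouched.

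**What to change.** In the SAP, replace the AHI rule by one of two options:

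1. Model the number of events with log(hours of sleep, or hours in the relevant position) as offset, in a negative binomial mixed model with the terms already listed.
2. Treat AHI, suitably transformed, as a quantitative endpoint under the existing rule for those endpoints.

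In either case include the baseline value, for consistency with that rule and with Outcomes {12} rather than to correct the SE. State how recordings with zero or very short supine time are handled and report their number by treatment. Present supine AHI together with the supine share of sleep, since supine time is itself changed by treatment. Apply the same to other per-hour indices only if they too are to be analysed as counts.

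The cost is wording. Total sleep time and the supine proportion are already listed PSG endpoints, so exposure is available. Event counts follow as index × hours if they are not recorded directly.
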